#### 3.2.3. Measurement Slots

Participants will be assessed three times: at baseline, the end of the intervention, and the end of the 6-month follow-up. At each time point, we will assess participants’ FMSs, PF, PA, and descriptive data (such as age, sex, weight, height) within one week. The executive plan of FMSs and PF is outlined in Figure 2.

### 3.3. Measurements

Primary and secondary outcome measures, and descriptive measures will be assessed in the three time slots. To reduce the loss of participants, researchers will inform teachers about the details of the measurements before the measurements start. Teachers will communicate with parents to avoid unnecessary loss of preschool children.

#### 3.3.1. Primary Outcome Measures

The primary outcomes in this study are FMSs and PF.

##### FMSs

Children’s FMSs will be assessed by a battery of tests from the Test of Gross Motor Development (TGMD) [42] and the Movement Assessment Battery for Children (MABC) [43]. The domain-specific content of FMS assessment was constructed in three phases. Phase 1 focused on the existing mature instruments for measuring FMSs. Three sub-domains represent FMSs competence: (a) locomotor skills, (b) object control skills, and (c) stability skills [8]. Within these subdomains, seven factors were postulated, comprising locomotor skills (i.e., 10-m shuttle run and hopping), object control skills (i.e., bouncing a ball, jamming coins, and kicking), and stability skills (balance beam and one-leg stand). Phase 2 involved a review of the existing FMS literature to identify each of the three subtest constructs. Phase 3 involved the use of a panel of experts to evaluate the FMSs measurements and consisted of a series of rounds before a final consensus is reached by the panel. After two rounds of the three-phase process, the three general domains representing FMSs were identified. The final pool of FMS assessment items includes measurements of running and hopping for locomotor skills; bouncing a ball, jamming coins, and kicking for object control skills; and the balance beam (for dynamic balance) and one-leg stand (for static balance) for stability skills (Table 2).

##### PF

We will use PF test kits (The PREFIT Battery) [2,44], which has been widely recognized and applied [2,45,46]. The PREFIT battery consists of measurements of the balance beam walk for assessing balance ability; handgrip and standing long jump for upper and lower limb strength, respectively; sit-and-reach for flexibility; 10-m shuttle run for agility; hopping for coordination; and 20-m shuttle-run for cardiorespiratory fitness (Table 3).

#### 3.3.2. Secondary Outcome Measures

The secondary outcome measure in this study will be PA.

PA will be assessed objectively using GT3X+ accelerometers (Pensacola, Fla., USA) and subjectively using the Preschool-age Children’s Physical Activity Questionnaire (Pre-PAQ) [47,48].

For the accelerometry, preschool children participating in this study will be instructed to wear the accelerometers over their waist consecutively for seven days, and will stop wearing them when they go to bed and during bathing and water activities. Teachers, parents, and preschool children will be instructed to take care of the devices and log the time when the devices are removed. Before being distributed to the children, the accelerometers will be set to record activity counts in 3 s epochs [49].

For the subjective self-reporting, we will use Pre-PAQ, which is a 37-item 3-day parent-reported questionnaire measuring the regular PA and sedentary behaviors of the parent and the preschool-aged child in the home environment. The Pre-PAQ has been shown to have acceptable validity and reliability in a sample of parents of preschool-aged children [50]. PA intensity and sedentary activity minutes will be analyzed separately according to the weekday or weekend.

### 3.4. Descriptive Measures

The descriptive measures in this study will be (1) sociodemographic characteristics; and (2) anthropometric data, including height, weight, and body mass index (BMI).

#### 3.4.1. Sociodemographic Characteristics

Parents will be instructed to complete a questionnaire about their child’s information including the date of birth and sex, household factors, family’s socioeconomic characteristics (family income, parental and primary guardian education, and parental employment status), child’s health status (reporting medical conditions and medications, if any), and child’s sleep time.

#### 3.4.2. Anthropometric Data

Standing height will be measured barefoot using a stable stadiometer (GMCS-SGZG3, Jian-Min, Beijing) to the nearest 0.001 m. Bodyweight with light clothes will be measured using a portable scale (GMCS-YERCS3, Jian-Min, Beijing) to the nearest 0.1 kg (kg). BMI was calculated by height and body weight:$$\mathrm{BMI}\;\left(\mathrm{kg}/m^{2}\right)=\frac{\mathrm{Weight}\;\left(\mathrm{kg}\right)}{{\left(\mathrm{Height}\right)}^{2}\;\left(m^{2}\right)}$$

## 4. Statistical Analysis

### 4.1. Sample Size

The primary outcome variables in this study are FMSs and PF. Before recruitment, a priori power analysis was performed in G*Power 3.1 to calculate the sample size necessary to detect meaningful changes from the baseline to the post-intervention time points in the total raw scores of seven FMSs (i.e., 10-m shuttle-run, hopping, bouncing a ball, jamming coins, kicking, balance beam, and one-leg stand) and seven PF (i.e., balance beam, handgrip, standing long jump, sit-and-reach, 10-m shuttle running, 20-m shuttle running, handgrip strength, and hopping). Using an alpha of 0.05 and a power of 80%, the calculation of the power to detect a pre-post change in these measures was based on the effect sizes reported in a recent systematic review. The expected effect size of the intervention on FMSs and PF was at 1.42 and 0.36 (standardized mean difference, SMD), respectively [51]. With reference to these results, a prudent estimation of the effect size (SMD = 0.36) was used for the calculation. The required sample was calculated to be 70. To account for the clustering effect, this number was then multiplied by a design effect (DE) of 1 + (*m* − 1) × ICC, where *m* is the average cluster size and ICC was estimated at 0.05. With an estimated average class size of 30, at least 150 participants will have to be recruited. Based on previous studies, we presumed a drop-out rate of 15%, implying a minimal sample size of 150/0.85 = 176 children in total. This study takes the class as the cluster of random sampling; the class size in recruited kindergartens is 30–35. Therefore, considering the drop-out rate and special samples (preschool children with developmental retardation or hyperactivity disorder), each experimental group was divided into two classes, implying about 60 children in each group. The total size is 300.

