Stability skills	Static balance (One-leg stand)	Material: stopwatch	Child stands on one foot with the supporting leg on the floor and the free leg flexed at the knees, maintaining the balance posture until the required posture cannot be maintained	The result will be recorded in seconds	

**Table 3 ijerph-19-06331-t003:** Physical Fitness Tests.

PF Proficiency	Test	Materials and Site Layouts	Directions	Performance Criteria	Cautions
Balance	Balance beam	As aforementioned in Table 2.			
Upper Limbs Strength	Handgrip	Materials: grip meter special for young children (TKK5825 TKK, in TAKEI, Japan).	Child squeezes gradually and continuously for at least 2 s or 3 s with one hand.	The result will be recorded in kilograms.	Testers adjust the grip meter for the optimal span for the child before the test.
Lower limbs strength	Standing Long Jump	Materials: tape measure, marking taps. Site Layout: a take-off line marked on the surface with taps.	Child will be instructed to stand with feet at shoulder width, and toes just behind the take-off line; then, child bends knees while swinging both arms, and pushes off vigorously and jumps as far as possible.	The reported distance is measured from the take-off line to the point where the back of the heel nearest to the take-off line lands on the ground. The result will be recorded in meters.	
Flexibility	Sit-and-reach	Material: sit-and-reach device.	Child will be instructed to take off their shoes, sit on the floor with legs fully extended, and press his/her feet against the base of the device. With arms fully extended and hands overlapped with palms down, child reaches as far forward as possible and pauses for 2 s.	The result will be recorded in centimeters.	Child will be required to stretch his/her lower back, hamstrings, and calves before the test.
Agility	10-m shuttle-run	As aforementioned in Table 2.			
Coordination	Hopping	As aforementioned in Table 2.			

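### The only scoring rule given for the two primary outcomes is a raw total that, taken literally, adds tests running in opposite directions and, for physical fitness, in different units

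*Protocol article*

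**What the plan says.** Section 3.3.1 of the protocol article states: "The primary outcomes in this study are FMSs and PF". It then lists the tests in each domain but gives no rule for turning seven results into one score. Section 4.4 models FMS and PF, again with no score defined.

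The only statement on aggregation is in section 4.1, where the power calculation targets "meaningful changes from the baseline to the post-intervention time points in the total raw scores of seven FMSs" and, in parallel, of seven PF tests. The FMS tests are "10-m shuttle-run, hopping, bouncing a ball, jamming coins, kicking, balance beam, and one-leg stand". The PF tests are "balance beam, handgrip, standing long jump, sit-and-reach, 10-m shuttle running, 20-m shuttle running, handgrip strength, and hopping"; handgrip appears twice in that list and is counted once here.

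Tables 2 and 3 say how each test is recorded. All seven FMS tests are recorded in seconds. Six are times to finish a fixed task. The seventh, the one-leg stand, is time held, with the child "maintaining the balance posture until the required posture cannot be maintained". In PF, the beam, 10-m run and hopping are carried over from Table 2 in seconds. For handgrip, "The result will be recorded in kilograms"; for the standing long jump, "The result will be recorded in meters"; sit-and-reach is in centimetres. The 20-m shuttle run has a rule for ending the test but no recorded unit. The article mentions no reversal of sign, standardisation or conversion to scaled scores.

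**The concern.** A raw total is interpretable only if every component points the same way and the units make the implied weights sensible. Neither holds for PF, and the first fails for FMS. A child who improves on every test moves some components down and others up, so the total may hardly change or may move the wrong way. In the PF total, 1 cm of reach counts as much as 1 m of jump, so the weights come from the choice of unit.

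Both primary outcomes are affected, and so is the second aim, which is to compare programmes. Table 1 gives the basic-movements arm 10 lessons aimed at stability. A gain there on the one-leg stand would push the FMS total against gains on the timed tasks, so the ranking of the arms could be distorted as well as power lost.

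**Working it through.** The plan gives no SDs, no correlations and no figure for the loss, so there is nothing of its own to reproduce. What follows is an illustration with stated assumptions.

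**Directions and units (Tables 2 and 3; directions inferred from the task descriptions)**

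| Domain | Lower is better | Higher is better | Units |
|---|---|---|---|
| FMS | 6: 10-m run, hopping, bouncing, coins, kicking, beam | 1: one-leg stand | seconds only |
| PF | 3: beam, 10-m run, hopping | 4: handgrip, long jump, sit-and-reach, 20-m run | s, kg, m, cm, one not stated |

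**Simple example.** Six timed FMS tests each 0.5 s faster: 6 × (−0.5) = −3.0 s. One-leg stand 3 s longer: +3.0 s. The FMS total changes by 0, although every test improved.

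**General formula.** Let test i have direction sᵢ (−1 or +1), standard deviation σᵢ, a true gain of d SDs over control, and a common correlation ρ between tests once directions are aligned.

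- As recorded: SMD = d·Σsᵢσᵢ / √[Σσᵢ² + ρ((Σsᵢσᵢ)² − Σσᵢ²)]
- Aligned: SMD = d·Σσᵢ / √[Σσᵢ² + ρ((Σσᵢ)² − Σσᵢ²)]

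Assumptions: d = 0.36 (the SMD used in section 4.1, applied to every test) and ρ from 0 to 0.5.

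**Equal SDs (σᵢ = 1)**

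- Aligned, either domain: 7 × 0.36 = 2.52. ρ = 0: 2.52/√7 = 0.95. ρ = 0.5: 2.52/√28 = 0.48.
- FMS as recorded, net count 6 − 1 = 5: 5 × 0.36 = 1.80. ρ = 0: 1.80/√7 = 0.68. ρ = 0.5: 1.80/√16 = 0.45.
- PF as recorded, net count 4 − 3 = 1: 0.36. ρ = 0: 0.36/√7 = 0.14. ρ = 0.5: 0.36/√4 = 0.18.

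With 60 children per arm and clustering ignored (so all powers are too high), power for PF is 11-17% as recorded against 74-99.9% aligned. For FMS it is 69-96% against 74-99.9%.

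**FMS when the one-leg stand varies more than each other test.** If its SD is k times theirs, the numerator as recorded is 0.36 × (k − 6).

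| k | SMD as recorded (size) | SMD aligned |
|---|---|---|
| 1 | 0.45-0.68 | 0.48-0.95 |
| 3 | 0.28-0.31 | 0.47-0.84 |
| 6 | 0.00 | 0.45-0.67 |
| 10 | 0.14-0.18, sign reversed | 0.43-0.56 |

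**Shared tests.** Section 3.3.1 uses "10-m shuttle run for agility; hopping for coordination" in PF, and both tests, with the beam, are also in FMS. For independent tests of equal variance, three shared out of seven give a correlation between the totals of 3/7 = 0.43.

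**The case against.** The strongest reply is that the article does not define the primary outcomes as sums. The phrase occurs once, in the sample-size rationale. The outcome section lists separate tests with separate recording rules, the analysis section names no composite, and the sentence after the phrase speaks of measures in the plural. It could mean the raw score of each test, and a fuller protocol or analysis plan may fix the scoring.

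Part of this stands: a reader may infer that the outcomes are formally defined as raw sums, and the article does not go that far. But the per-test reading leaves the word total without work to do. Section 4.1 attaches one expected effect to FMS (1.42) and one to PF (0.36), and section 4.4 uses a single FMS capacity and a single PF level as baseline covariates. The text states a rule and gives no other, so this is more than omitted detail.

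The second reply concerns size. A reader might count directions and conclude that FMS keeps 5/7 of its effect and PF only 1/7, a loss of 86%. Those fractions are effect-size losses only for uncorrelated tests with equal SDs. At correlation 0.5 and equal SDs the loss is about 5% for FMS (0.45 against 0.48) and 62% for PF (0.18 against 0.48).

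The third reply is that the shared tests are openly declared and bias neither group comparison. That is right. The interaction named in section 4.4 is between exercise and the outcomes; only the abstract speaks of interactions between the domains.

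**Conclusion.** The point holds in limited form. The one stated scoring rule, followed literally, yields totals without a consistent direction in both domains and with arbitrary weights in PF. Such totals can mask a true benefit and, under some SDs, reverse it.

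It is not shown that benefit will cancel. With equal SDs the FMS loss is modest, while the PF loss is large throughout the range examined. FMS cancels completely only if the one-leg stand's SD is about six times that of each other test, and the article gives no SDs to say whether that is so. Mixed units are a PF problem only. All the figures rest on equal gains of 0.36 SD, a common correlation of 0 to 0.5 and the stated SD ratios. The overlap of three tests is a minor matter, relevant only to an association between FMS and PF.

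**What to change.** Before outcome data are examined, replace the raw totals in section 4.1 and define the score in section 3.3.1: for each domain, the mean of the seven test z-scores, each standardised on the baseline mean and SD pooled over all arms, with the sign reversed for the timed tests where lower is better (six in FMS, three in PF; the one-leg stand is not reversed). State the recorded unit of the 20-m run. Report each test separately as secondary. In any analysis of the association between FMS and PF, count the beam, 10-m run and hopping in one domain only.

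A cap on the one-leg stand is not part of this fix, since the article offers no value or basis for one.

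The cost is wording: the same tests, visits and data. The downside is that the composite is in SD units, which the separate test results offset.

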### 4.4. Data Analysis Plan

Baseline characteristics and unadjusted study outcome measures will be summarized by intervention groups using descriptive statistics and used to assess between-group equivalence at baseline. Prespecified baseline covariates in both primary and secondary outcome analyses will include age, sex, FMSs capacity, PF level, and PA level.

Baseline demographic descriptors and primary and secondary outcome measures will be compared across groups by using analysis of variance (a non-parametric test will be used when the data does not conform with a normal distribution) for continuous variables and the χ^2^ test for categorical variables. The planned descriptive data on measured-point FMSs and PF will be tabulated across the intervention groups and control group. In our primary analysis of the FMSs and PF outcome, we will use mixed model analyses to estimate the differences with their corresponding 95% CIs, comparing the BA, RA, BM, and MA groups with the control group. Time, physical exercise programs (intervention or control groups), and their interaction will be fixed factors. The random effects will be the kindergarten and individual to take into account the clustered data structure.

Multilevel linear regression models will be constructed to assess the effectiveness of the physical exercises on FMSs and PF performance. The baseline data of the outcome variables, assessment points, intervention groups, and any imbalanced covariance will be added to the model along with the kindergartens and PA as random effects. The interaction between physical exercise and FMSs and PF will be tested.

Secondary analyses will investigate the effect of the intervention on other domains using different types of regression analyses, depending on the outcomes. Logistic regressive analyses will be constructed to assess the interference factors. The models will be used to assess the effect of forms of physical exercise, and to explore associations between secondary outcome measures, and will be adjusted for various confounding factors (e.g., sex, PA).

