## 7. Challenges and Limitations

The current protocol has some challenges. First, the participants in this study are 4-–5-year-old preschool children who still largely lack self-control and attentional focus. It will, therefore, be difficult to engage them continuously in the designed physical exercise program. To meet this challenge, the research group will staff each intervention group with two researchers to ensure preschool children’s safety and the intervention quality. Second, the intervention will last for 16 weeks, which will place a great human resource pressure on the PEFP group. We plan to stagger the intervention time of two close kindergartens, and the intervention will be carried out between 8:30 and 11:30 in the morning. In this way, the researchers assigned by the PEFP group can assist more intervention groups within the time allowed.

There are some limitations to this protocol. First, young children are in a rapid period of growth and development; thus, it will be difficult to identify whether natural growth or the exercises intervention contributes to the improvement in children’s FMSs and PF. Like other studies, this protocol will set up a control group in the same school with each intervention group to reduce the confounding impact of natural growth as much as possible. Second, the intervention in this study will last 16 weeks, which seems insufficient to improve FMSs and PF. However, the duration of FMSs or PF interventions in previous studies varied from eight weeks to one academic year or longer [32,41,52,53].

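### The 80% power in section 4.1 is for a pre-post change, not for the primary arm-versus-control comparison, where power for PF at SMD 0.36 is well below 80%

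*Protocol article*

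**What the plan says.** Section 4.1 (Sample Size) sets the error rates: "Using an alpha of 0.05 and a power of 80" per cent. The quantity powered is "the calculation of the power to detect a pre-post change in these measures". On effect sizes it says "The expected effect size of the intervention on FMSs and PF was at 1.42 and 0.36" as SMDs, and that "a prudent estimation of the effect size (SMD = 0.36) was used for the calculation". Then "The required sample was calculated to be 70". This is multiplied by a design effect with class size 30, where "ICC was estimated at 0.05", giving 150, and divided by 0.85 for drop-out, giving 176. The planned total of 300 comes from two classes, about 60 children, in each of five groups.

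Section 4.4 (Data Analysis Plan) describes the primary analysis of FMSs and PF as a mixed model "comparing the BA, RA, BM, and MA groups with the control group". Its fixed effects are time, programme and their interaction. Its random effects are kindergarten and individual.

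Section 7 (Challenges and Limitations) says of children this age that "it will be difficult to identify whether natural growth or the exercises intervention contributes to the improvement".

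**The concern.** The calculation and the primary analysis address different quantities. Over 16 weeks children in every arm, control included, can be expected to improve by growth alone, as section 7 recognises. Power to detect a pre-post change therefore does not tell the reader whether the trial can separate a programme from unorganized activity. That separation is the first aim of the study.

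The total of 300 does not close the gap, because it follows from class counts and not from a between-arm calculation. PF is one of the two primary outcomes, and 0.36 is the effect the plan itself chose as prudent. As written, section 4.1 attaches 80% power to that effect. The primary contrast does not have it, and wide PF intervals would come as a surprise to anyone relying on the stated figure.

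**Working it through.** **The plan's own figures first**

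- Paired test, d = 0.36, two-sided 5%, power 80%. Normal approximation: ((1.960 + 0.842)/0.36)² = 60.6, so 61. Noncentral t: 63 (one-sided: 50). The stated 70 is not reproduced.
- Design effect: 1 + (30 − 1) × 0.05 = 2.45. 70 × 2.45 = 171.5, not 150. (61 × 2.45 = 149.45 would round up to 150.)
- Drop-out: 150/0.85 = 176.5, which agrees with the stated 176. Carried through from 70, the result would be 171.5/0.85 = 201.8, so 202.

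**Primary contrast: one arm versus control, PF**

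Inputs from section 4.1: SMD 0.36, two-group alpha 0.05, ICC 0.05, two classes and about 60 children per arm, 15% loss.

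Assumptions not in the document: a two-sided test; 0.36 read as a between-arm difference; baseline correlation r of 0, 0.5, 0.7 or 0.8; and either 5 degrees of freedom (10 classes − 5 arms) or normal quantiles.

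1. Without clustering, 80% power needs 2 × (2.802/0.36)² = 121.1, so 122 per arm (123 by noncentral t). The plan has about 60.
2. After loss: 60 × 0.85 = 51 per arm, or 25.5 per class.
3. Design effect: 1 + (25.5 − 1) × 0.05 = 2.225. Effective n per arm: 51/2.225 = 22.9.
4. Noncentrality: λ = (0.36/√(1 − r²)) × √(22.9/2). Power is the two-sided rejection probability at λ. The critical value is 2.571 with 5 df and 1.960 with normal quantiles.

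| r | λ | Power, 5 df | Power, normal |
|---|---|---|---|
| 0 | 1.22 | 17% | 23% |
| 0.5 | 1.41 | 21% | 29% |
| 0.7 | 1.71 | 28.5% | 40% |
| 0.8 | 2.03 | 38% | 53% |

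5. SMD detectable with 80% power, for r = 0, 0.5 and 0.7: 1.04, 0.90 and 0.74 with 5 df; 0.83, 0.72 and 0.59 with normal quantiles.

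**Sensitivity**

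- No loss (60 per arm, design effect 2.45): 18-40% with 5 df and 24-56% with normal quantiles, over the same r.
- Kindergarten as the cluster with 51 children per arm: design effect 1 + 50 × 0.05 = 3.5 and effective n 14.6. Normal-quantile power is 16% at r = 0 and 37% at r = 0.8. If each arm is a single kindergarten, there are no between-cluster degrees of freedom within arms, and power is undefined.

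**FMSs**

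At SMD 1.42 with effective n 22.9 and r = 0, power is about 97% with 5 df and above 99% with normal quantiles.

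**The case against.** The strongest reply is that the time-by-programme interaction in section 4.4 is itself a difference in pre-post change, so the powered quantity is related to the primary analysis. That stands in part: the calculation is incomplete rather than irrelevant. It still leaves out the control arm's change and its variance, so it does not give the power of the contrast.

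A second reply is that any single power figure depends on inputs the document does not fix. This stands in full. A reader might quote one narrow band, such as 17-29%, but that needs 5 degrees of freedom and a baseline correlation of at most 0.7, and the document states neither. The unit is also unsettled. Sections 2.1 and 4.1 name the class as the cluster. Section 2.3 allocates kindergartens. Section 4.4 has a kindergarten random effect but none for class. Section 7 places a control group in the same school as each intervention group. Only a range under stated assumptions is defensible.

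Other stronger readings are tempting but unsupported:

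- That 70 came from entering the SMD as a different effect-size index in an ANOVA routine. Section 4.1 names the software but not the test, so the origin of 70 cannot be established.
- That a null PF result would be reported as no effect. Section 4.4 already plans differences with 95% CIs.
- That comparisons between active arms are weaker because their differences are smaller. The document gives no size for those differences.

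**Conclusion.** The concern holds for PF. The stated 80% power does not apply to the primary arm-versus-control comparison, and no power is stated for that comparison. With the class as the unit and the plan's own ICC, arm size and loss, PF power at 0.36 is about 17-38% (5 df) or 23-53% (normal quantiles) for baseline correlations of 0 to 0.8. No clustered variant tried comes near 80%. The exact figure rests on the assumed correlation, degrees of freedom and unit. The conclusion that it is well below 80% does not.

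A reader might infer that both primary outcomes are underpowered. The document does not support that: at its own SMD of 1.42, FMSs are adequately powered with the class as the unit.

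Separately, 70 and 150 do not follow from their stated inputs. Correcting 150 would raise the stated minimum from 176 to 202, still below the planned 300, so that slip alone does not change enrolment.

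**What to change.** 1. Reconcile the unit of randomization (class or kindergarten) across sections 2.1, 2.3, 4.1, 4.4 and 7. The power cannot be restated safely before this.
2. Replace the pre-post calculation in section 4.1 with one for the arm-versus-control difference at 16 weeks. State the SMD as a between-arm difference, the ICC, clusters per arm, degrees of freedom, baseline correlation and loss. Correct or remove the 70 and 150.
3. Restate what 300 children give for PF as a range under those assumptions, with the detectable SMD. With the class as the unit this is about 0.74-1.04 (5 df) or 0.59-0.83 (normal quantiles), for r from 0.7 down to 0.
4. Drop the 80% claim for PF, and say that PF conclusions rest on estimates and 95% CIs. Give FMS power separately.

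The cost is a rewritten section 4.1, consistent wording on the unit elsewhere, and a less favourable stated figure for PF. The power restatement itself calls for no extra enrolment and no operational change.

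### Section 4.1: the sample-size chain 70 → 150 → 176 does not follow from its own design effect of 2.45; either the 70 or the 150 is wrong

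*Protocol article*

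**What the plan says.** Everything is in section 4.1 (Sample Size) of the protocol article.

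- The calculation is described as one for a pre-post change. Its error rates are given as "Using an alpha of 0.05 and a power of 80" per cent, and for the effect size "a prudent estimation of the effect size (SMD = 0.36) was used for the calculation".
- The result before clustering is "The required sample was calculated to be 70".
- For clustering, "this number was then multiplied by a design effect (DE) of 1" plus the product of the ICC and one less than the class size. On these two inputs, the section says that *m* "is the average cluster size and ICC was estimated at 0.05".
- The clustered result is "With an estimated average class size of 30, at least 150 participants will have to be recruited".
- A 15% drop-out rate is then applied, "implying a minimal sample size of 150/0.85 = 176 children in total".
- The section ends by setting two classes per group, about 60 children per group and 300 in total.

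**The concern.** The starting value, the formula, both of its inputs and the result are all printed within a few sentences, and they disagree. This is not detail left to a fuller document: a reader with only section 4.1 can do the multiplication and does not get 150.

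The 150 feeds directly into 176, the only minimum that the article states. If the 70 is right, that minimum is too low on the plan's own assumptions, and the margin between it and the planned 300 looks wider than it is. If the 70 is wrong, the article misreports the output of its power calculation. Either way the sample-size justification for the primary outcomes cannot be reproduced as printed.

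**Working it through.** **Inputs, all from section 4.1:** unadjusted sample 70; m = 30; ICC = 0.05; drop-out 15%, applied as N/(1 − 0.15); SMD 0.36; alpha 0.05; power 80%.

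**1. The plan's own figures.** The drop-out step is consistent with its input: 150/0.85 = 176.5, printed as 176 (177 if rounded up, as is usual for a minimum). The design-effect step is not:

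- DE = 1 + (30 − 1) × 0.05 = 2.45
- 70 × 2.45 = 171.5, rounded up to 172
- printed: 150

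**2. Carrying the stated inputs through.** 172/0.85 = 202.4, rounded up to 203. If 171.5 is carried unrounded, 171.5/0.85 = 201.8, rounded up to 202. The printed figure is 176.

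**3. Size of the gap if 70 is right.** Before drop-out: 172 − 150 = 22, and 22/172 = 13%. After drop-out: 203 − 176 = 27, and 27/203 = 13%. The planned 300 is 1.70 times 176 but 1.48 times 203.

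**4. What would produce 150?**

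| Quantity changed | Value needed | Stated value |
|---|---|---|
| Design effect, with n = 70 | 150/70 = 2.14 | 2.45 (from m and ICC) |
| ICC, with n = 70 and m = 30 | (2.14 − 1)/29 = 0.039 | 0.05 |
| m, with n = 70 and ICC = 0.05 | 1 + (2.14 − 1)/0.05 = 23.9 | 30 |
| Starting n, with DE = 2.45 | 150/2.45 = 61.2 | 70 |

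Rounding does not bridge any of these gaps.

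**5. Is a starting value near 61 plausible?** The section does not give the sidedness of the test; assume two-sided. For a paired pre-post comparison at SMD 0.36, the normal approximation is n = (1.960 + 0.842)²/0.36² = 7.85/0.1296 = 60.6, so 61. Then 61 × 2.45 = 149.5, or 150. The paired t-test gives 62.5, so 63, and 63 × 2.45 = 154.4. A slip in the 70 is therefore a credible source of the mismatch, but it is not proved.

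**The case against.** The strongest reply is that nothing operational depends on this step. The Abstract and section 4.1 both fix the total at 300, which is above 176 and above 203. That stands: this is a correction to the stated minimum and its margin, and planned enrolment is unaffected.

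Four stronger readings are tempting, and the document does not support them.

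- *The minimum should be 203.* A reader might infer this from the multiplication alone. It holds only if 70 is correct. Since about 61 reproduces the 150, the error may lie in the 70, and then 172 and 203 have no basis.
- *The minimum should be higher still, because classes are larger than 30.* The section does say that "the class size in recruited kindergartens is 30–35". At m = 35 the design effect would be 2.70, giving 189 and then 223. But the formula takes the average class size, which is stated as 30 and agrees with two classes making about 60 per group. The top of a range is not that average.
- *176 is a floor for stopping recruitment or judging class closure.* No section says so. Section 3.2.2 handles suspension by a two-week criterion and a decision of the project leader, with no reference to sample size.
- *Planned enrolment is too small because of this slip.* That does not follow with the class as the cluster, as sections 2.1 and 4.1 have it. Section 2.3 instead speaks of kindergartens being assigned as units. If the cluster were about 60 children, the design effect would be 3.95, giving 277 and then 326, above 300. That rests on a different reading of the unit of allocation, not on this arithmetic.

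**Conclusion.** The inconsistency is certain on the printed inputs: 70, a design effect of 2.45 and 150 cannot all be right, and no stated class size or ICC reconciles them. Which figure is wrong cannot be settled from the document.

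- If 70 is right, the clustered minimum is 172, and 203 after drop-out (202 without intermediate rounding).
- If 70 is the error and about 61 was meant, 150 stands, and the only further change is one child, 176 to 177.

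Both branches take the class as the cluster, the stated m and ICC, and 15% drop-out; the second also assumes a two-sided paired calculation by the normal approximation. In both, 300 exceeds the minimum. Correcting the chain does not settle whether a pre-post change is the right basis for a trial that compares arms; that is a separate question, and a corrected minimum should not be read as answering it.

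**What to change.** Go back to the power-calculation output, state which figure is in error, and reprint the chain once in section 4.1, with the design effect of 2.45 shown explicitly.

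- If 70 stands: replace 150 with 172, and replace the drop-out line with 172/0.85 = 203.
- If 70 is the error: correct the 70 (about 61 gives 150), keep 150, and print 150/0.85 as 177.

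State the sidedness of the test and the rounding rule so that the figures can be reproduced. The cost is about two numbers in one paragraph; the planned total of 300 need not change for this step.
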